## Abstract

**Background::**

Patients with esophageal cancer suffer from anxiety in the perioperative period surrounding esophagectomy; this may increase the risk of postoperative complications. In particular, postoperative aspiration pneumonia carries a high risk of hospital mortality. Bukuryoingohangekobokuto (BRIHK) is a traditional Japanese medicine formula used to treat anxiety, the feeling of a foreign body in the esophagus, and water brash. We hypothesize that BRIHK might be effective for both anxiety and water brash in perioperative patients with esophageal cancer. The aim of this study is to evaluate the efficacy and safety of BRIHK compared to a placebo for anxiety and water brash in perioperative esophageal cancer patients.

**Method/design::**

This will be a single-center, single blind, placebo-controlled randomized clinical trial. Twenty-four patients with esophageal cancer undergoing radical resection surgery will be registered to participate, then randomly and blindly assigned to the BRIHK treatment group or control group. Patients will be administered BRIHK or the placebo from 2 weeks before to 6 weeks after surgery. Primary outcome measures will be anxiety and depression (assessed using the Hospital Anxiety and Depression Scale), and water brash (assessed using the 10-item Eating Assessment Tool, Esophagus and Stomach Surgery Symptom Scale, and videofluoroscopy swallowing measurement). Incidences of aspiration pneumonia will be noted and abdominal gas volume, inflammatory markers, and nutrition status will be evaluated.

**Discussion::**

This investigative study will provide clinical evidence of BRIHK administration for anxiety and water brash, which might improve mental distress and reduce postoperative mortality.

**Trial registration::**

The protocol and progress are registered on the Japan Registry of Clinical Trials (jRCT s021190001) and University Hospital Medical Information Network (UMIN000031330). The protocol was approved by the Japanese Ministry of Health, Labour and Welfare certified clinical research review board, Tohoku University (CRB2180001).

## Introduction

1

Patients diagnosed with fatal cancer have a greater risk of developing anxiety than the general population.^[1]^ In patients referred for surgery, the most common factors contributing to anxiety are concern about family and fear of complications, results of the operation, and postoperative pain.^[2]^ Preoperative anxiety is associated with increased anesthetic requirements,^[3]^ increased pain,^[4]^ nausea and vomiting,^[5]^ and prolonged hospitalization^[6]^ in the postoperative period. Previous articles have reported that 34% of patients with esophageal cancer have possible or probable anxiety prior to surgery,^[7]^ and 16% to 34% of postoperative patients still have anxiety during the follow-up year after diagnosis.^[8]^ Anxiety is a clinical issue in the perioperative period.

Esophagectomy is a standard surgical procedure for the treatment of esophageal cancer. Its morbidity and mortality rates after surgery have decreased in recent decades, but remain higher than those of other thoracic surgical procedures.^[9]^ In particular, postoperative pneumonia is one of the most common and fatal complications after surgery, occurring in 9% to 19% of patients even in recent reports,^[10–13]^ and is a major risk factor of hospital mortality. In a videofluoroscopic swallowing study, 32% of postoperative esophageal cancer patients showed evidence of subglottic aspiration, which is an important preliminary risk of aspiration pneumonia.^[14]^ As such, prevention of postoperative pneumonia is a clinical issue in esophageal cancer surgery.

Together with Western medicine, traditional Japanese (Kampo) medicine has been widely used in Japan for the treatment of both mental and physical disorders. Bukuryoingohangekobokuto (BRIHK) is used for patients with anxiety, depressed feelings, the feeling of a foreign body in the throat and esophagus, nausea, heartburn, nervous gastritis, water brash, and more.^[15]^ Hangekobokuto, which is included in BRIHK, has been reported to improve the impaired swallowing reflex^[16]^ and reduce the risk of pneumonia and pneumonia-related mortality in clinical trials of elderly patients.^[17]^ A recent trial showed hangekobokuto prevented aspiration pneumonia in patients undergoing cardiovascular surgery.^[18]^

We hypothesize that BRIHK administration in the perioperative period could alleviate anxiety and reduce water brash in patients who undergo esophagectomy. This protocol outlines a study aimed to investigate the efficacy and safety of BRIHK for anxiety and water brash, that is, aspiration during the postoperative period in esophageal cancer patients.

## Methods/design

2

### Study design and setting

2.1

The study will be a single-center, single blind, parallel randomized controlled trial to assess the efficacy and safety of BRIHK for anxiety and postoperative water brash in esophageal cancer patients. Participants will be blind to the treatment assignment throughout the trial. The study design is shown in Figure 1.

**Figure 1 F1:**
[figure not shown]
Study design: single-blind placebo-controlled randomized clinical trial.

### Eligibility

2.2

Those who meet all the following inclusion criteria and do not meet any listed exclusion criteria will be eligible to participate.

#### Inclusion criteria

2.2.1

1.Scheduled to undergo elective radical resection surgery for esophageal cancer in the upper, middle, or lower parts2.Pre-treatment clinical stage II, III, or IVa according to the 8^th^ edition of the Union for International Cancer Control TNM classification (except for T4b and N3)^[19]^3.Eastern Cooperative Oncology Group performance status of 0, 1, or 24.Hospital Anxiety and Depression Scale (HADS) score ≥ 8^[20]^5.Aged ≥ 20 years at the time of consent6.Either sex7.Provision of written informed consent

#### Exclusion criteria

2.2.2

1.History of abdominal surgery (except for appendectomy or caesarean section) or ileus2.Inflammatory bowel diseases3.Undergoing emergent surgery for esophageal cancer4.Concomitant use of prohibited medicine 4 weeks before inclusion5.Past history of radiotherapy or chemotherapy for esophageal cancer6.Allergy to Kampo formulas or intolerance to lactose (major excipients of Kampo formulas)7.Severe liver, kidney, cardiovascular, blood, or metabolic diseases8.Pregnant, within 28 days after childbirth, or breastfeeding9.Dementia10.Difficulty with study participation as judged by the researchers

Prohibited medicines in this study include Kampo formulas other than BRIHK and psychotropic agents. Temporary use of hypnotics will be allowed if needed.

### Interventions

2.3

In study arm P (placebo group), 2.5 g of lactose powder (Pfizer Japan Inc, Tokyo, Japan) will be orally administered 3 times daily before meals from 14 days before surgery to 42 days after surgery. On the day of the operation, administration will be stopped. During the fasting period after surgery, lactose will be dissolved in warm water and administered through an intestinal tube via the transintestinal fistula. Lactate is set as a non-active ingredient.

In study arm A (BRIHK group), 2.5 g of BRIHK will be orally administered 3-times daily before meals on the same schedule and using the same methods as in arm P. BRIHK is a multicomponent formula, originally extracted from 9 crude drugs as follows: 6 g Japanese Pharmacopoeia (JP) Pinellia tuber, 5 g JP Poria sclerotium, 4 g Atractylodes lancea rhizome, 3 g JP Magnolia bark, 3 g JP Citrus unshiu peel, 3 g JP Ginseng, 2 g JP Perilla herb, 1.5 g JP Immature orange, and 1.0 g JP Ginger (JP: the 17th Japanese Pharmacopoeia^[21]^). It is currently prepared for prescription use in Japan as granules through the process of decoction, concentration, drying, and the addition of excipients (Tsumura BRIHK extract granules for ethical use, Tsumura & Co., Tokyo, Japan).^[15]^

We will place a label on both the packages of lactose and BRIHK for blinding. We will monitor the participants’ adherence by having them return unused medication.

### Outcomes

2.4

The primary outcome measures include mental status and water brash before and after surgery. Mental status will be assessed using HADS, which contains both anxiety and depression subscale scores.^[15]^ Water brash will be assessed using the 10-item Eating Assessment Tool (EAT-10), Esophagus and Stomach Surgery Symptom Scale (ES4) and videofluoroscopy swallowing measurement. EAT-10 is a screening assessment scale for dysphagia.^[22]^ ES4 measures the postoperative symptoms of esophagogastric cancer.^[23]^

Secondary outcome measures include the incidence of aspiration pneumonia, number of postoperative hospitalization days, abdominal gas volume, plasma inflammatory markers, chest computed tomography findings, nutritional status, and laboratory examination findings. Aspiration pneumonia will be diagnosed based on the clinical practice guideline for pneumonia.^[24]^ Abdominal gas volume will be measured by analyzing an abdominal radiograph using Koide methods with Image J.^[25,26]^ White blood cell count, serum interleukin-6, tumor necrosis factor α, and granulocyte-colony stimulating factor will be measured as inflammatory markers. Serum albumin, prealbumin, total cholesterol, retinol-binding protein, transferrin, C-reactive protein, and lymphocytes will be measured as nutrition status markers. We will also evaluate body weight, body mass index, triceps skinfolds, and arm muscle circumference measured using bioelectrical impedance analysis (InBody 770, InBody, Soul, Korea).

Secondary safety measurements will include adverse events, side effects of BRIHK, and laboratory data abnormalities exceeding postoperative change. BRIHK has a possible side effect of hypersensitivity (e.g., rash or urticaria).^[15]^ We will routinely examine the laboratory data for postoperative adverse events such as those involving liver function, kidney function, electrolytes, creatine phosphokinase, glucose, and brain natriuretic peptide.

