### Data collection

2.9

All data will be collected and recorded on a paper-based case report form by the investigators. Patient characteristics, the questionnaires, and evaluation forms such as HADS, EAT-10, ES4, as well as the findings of videofluoroscopy swallowing measurement and CT, abdominal gas volume, laboratory data, and physical status will be collected. Adverse effects will also be recorded. After recording the data, the investigators will confirm the case report form, referring to its source documents.

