### Statistical methods

2.11

The primary statistical analyses will be performed by WDB Clinical Research Co., Ltd. using the full analysis data set, from which patients who withdraw consent before assessment of the primary endpoint will be excluded. In addition, we will repeat the analyses in the per-protocol set, which will exclude patients with major protocol deviation. The safety analysis will be performed using the complete data set in the BRIHK group.

For baseline characteristics variables, summary statistics will be calculated using frequencies and proportions for categorical data; means, standard deviations, medians, and quartiles will be used for continuous values. Patient characteristics will be compared using the Chi-squared test or Fisher exact test for categorical valuables and the Wilcoxon rank-sum test for continuous valuables. For the primary intra-group analysis, we will calculate mean HADS and ES-4 scores for each timepoint with 95% confidential intervals and compare the HADS and ES-4 scores at the baseline with those during the treatment period using Wilcoxon signed-rank test. For the inter-group analysis, we will calculate the change in the HADS and ES-4 scores from the pre- to post-treatment period and compare them between the 2 groups using Wilcoxon signed rank test. Then, we will perform an analysis of covariance with the covariates of patient characteristics and calculate the confidence interval. For the analyses of secondary outcome measures between the 2 groups, we will perform the Chi-squared test or Fisher exact test for categorical valuables and Wilcoxon rank-sum test for continuous valuables. *P* values less than 5% will be considered statistically significant, and we will not adjust *P* values in multiple comparisons.

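### The laboratory safety measure uses an undefined surgical yardstick that fits the 14 preoperative dosing days poorly, and it is analysed without the placebo arm

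*Protocol article*

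**What the plan says.** Section 2.4 (Outcomes) of the protocol article names three safety items: "Secondary safety measurements will include adverse events, side effects of BRIHK, and laboratory data abnormalities exceeding postoperative change". The last item alone, "laboratory data abnormalities exceeding postoperative change", carries a surgical qualifier. Section 2.4 then describes the routine review in these terms: "We will routinely examine the laboratory data for postoperative adverse events such as those involving liver function, kidney function, electrolytes", with further analytes following. Neither sentence gives a reference value, a threshold or a time window.

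Section 2.3 (Interventions) gives product in both arms "from 14 days before surgery to 42 days after surgery", with none on the day of the operation. The abstract agrees: "from 2 weeks before to 6 weeks after surgery".

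Other parts of the article also deal with laboratory data:
- Section 2.4 lists among the secondary outcomes "nutritional status, and laboratory examination findings", without the qualifier.
- Section 2.9 (Data collection) states "abdominal gas volume, laboratory data, and physical status will be collected", with no limit to the postoperative period.
- Section 2.11 (Statistical methods) sets between-arm tests "For the analyses of secondary outcome measures between the 2 groups". The same section says that the safety analysis uses the data of the BRIHK group.
- Section 2.13 (Harms) covers adverse events and other unintended effects of the interventions, with no time limit.
- Section 2.1 says that participants are blind to assignment and says nothing of investigators.

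**The concern.** A laboratory safety measure should pick up a drug effect wherever in the exposure period it arises. This one is tied to surgery, although exposure begins two weeks earlier. Those two weeks are the only part of the exposure without surgical confounding, so a laboratory effect of the product would be easiest to recognise there. The criterion does not say how an abnormality in that period is to be classed.

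After surgery the criterion acts as a filter. Someone has to decide, case by case, what surgery alone would have produced, and abnormalities judged to fall within that range do not enter the measure. With no written reference, the decision may differ between assessors and may be influenced by knowledge of the arm. If product adds to an expected postoperative rise without taking it outside what is thought usual, this measure does not register it. Safety is part of the trial's stated aim, so the laboratory safety result should not depend on an unwritten judgment.

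**Working it through.** The article gives no laboratory threshold or event rate. The check is therefore a reading of the sections against each other, with one piece of arithmetic on the dosing period.

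**1. Share of dosing before surgery.** Inputs from section 2.3: 14 days before surgery, 42 days after, none on the operation day.
- Dosing days = 14 + 42 = 56.
- Preoperative share = 14 / 56 = 0.25, or 25%.
- Cross-check with the abstract: 2 weeks × 7 = 14 days and 6 weeks × 7 = 42 days. The two places agree.

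**2. Does the criterion have a meaning in that quarter?** A change after surgery cannot be the yardstick for a value drawn before surgery. Two readings are possible. Either a preoperative abnormality falls outside the criterion, or it counts because surgery cannot explain it. The text does not choose between them. The routine-review sentence does not help, since it mentions only events after surgery.

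**3. What happens after surgery?** Here the wording is clear: an abnormality must go beyond surgical change to count. One judged to lie within it does not enter this measure. What remains open is how large that change is, and against which value it is judged.

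**4. Who can make the judgment?** Section 2.9 has the investigators collect and record the data. Section 2.1 states blinding for participants only. Nothing in the article keeps the judgment from being made with knowledge of the arm.

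**5. What could supply the missing yardstick?** The placebo arm has the same operation on the same schedule. With 24 patients allocated 1:1 (sections 2.7 and 2.8), that is 24 / 2 = 12 patients per arm. Section 2.11 limits the safety analysis to the BRIHK group, so about 12 patients are assessed against a notion of usual surgical change, while about 12 concurrent patients who show that change are left out of the analysis.

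**6. What reaches the report by other routes?**

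| Route | Surgical filter? | Limited to after surgery? | Both arms? |
|---|---|---|---|
| Laboratory abnormality measure (2.4, 2.11) | Yes | Unclear | BRIHK only, on the safety-analysis sentence |
| Laboratory findings as secondary outcome (2.4, 2.11) | No | Not stated | Yes |
| Laboratory data on the case report form (2.9) | No | No | No restriction stated |
| Adverse events (2.4, 2.13) | No | No | Recording not restricted by arm; safety analysis BRIHK only |

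The fault is thus confined to the first row.

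**The case against.** The strongest reply is that the surgical qualifier attaches to one of three safety items. Adverse events and side effects of BRIHK carry no such condition, and section 2.13 extends to unintended effects of any kind and refers causality to a monitoring board. A liver or electrolyte abnormality before surgery can be recorded there. Unfiltered laboratory findings are also a secondary outcome and are compared between arms. This stands, and it limits the harm considerably.

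A reader might infer more than the article supports, in three ways:
- *That laboratory abnormalities before surgery, or within surgical change, are thrown away.* They are not. The values are collected and can be reported by the other routes in the table above.
- *That preoperative abnormalities are excluded by definition.* The text does not say so. A rise before surgery can be read as one that surgery does not explain.
- *That a drug effect is absorbed into a baseline drawn after 14 days of product.* No section sets the laboratory reference in that way. The sampling schedule is in Figure 2, which is not available here, so its content cannot be held against the plan.

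It is also fair to say that grading scales and table layouts usually belong in the full protocol or the analysis plan, and their absence from an article is no fault.

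The other routes do not fully replace the measure, however. Section 2.13 does not say when a laboratory value becomes an adverse event, and the only laboratory-abnormality criterion given is the filtered one. A rank test on about 12 patients per arm can miss one or two marked individual abnormalities, which a tabulation of abnormalities is meant to show. The qualifier is also a stated rule that does not fit the stated dosing period, which is different from a detail left for later.

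**Conclusion.** The point holds for the single laboratory safety measure in section 2.4. Its yardstick is undefined and does not suit 14 of the 56 dosing days (25%). After surgery, it leaves out abnormalities judged to lie within surgical change. That judgment is not protected by any stated blinding of investigators, and the arm that could inform it is outside the safety analysis.

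The 25% is the calendar share of dosing to which the criterion is ill suited. It does not measure lost data or bias, and the article does not allow either to be estimated. It assumes dosing as scheduled in section 2.3.

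The conclusion rests on two readings. First, the safety-analysis sentence in section 2.11 governs the laboratory safety measure. If the between-arm rule for secondary outcomes is meant to apply instead, the objection about the placebo arm falls away, but the undefined filter remains. Second, the full protocol does not define the phrase elsewhere. The matter should be corrected because the cost is low and safety is a stated aim. It does not show that safety data are being suppressed.

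**What to change.** In section 2.4, define the measure as any laboratory abnormality from the first dose to the end of data collection, judged against the value before the first dose, and remove the surgical filter. Extend the routine-review sentence to the whole dosing period, so that it no longer mentions postoperative events alone. In section 2.11, tabulate this measure in both arms, with separate columns for before surgery (first dose to operation) and after surgery.

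Use the samples already scheduled. If Figure 2 contains an on-treatment sample before the operation, it fills the preoperative column. If it does not, the table should say so.

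The cost is a rewording of two sections and one added table, with no new procedure and no change to treatment. The small downside is a longer list of abnormalities of surgical origin. Showing the placebo arm alongside makes that list interpretable, so the filter should not be removed without adding that arm.

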### Participant timeline

2.5

The time schedule for this trial and data collection is summarized in Figure 2.

**Figure 2 F2:**
[figure not shown]
Time schedule.

### Sample size

2.6

There is no clinical evidence regarding the treatment effects of BRIHK for anxiety or water brash. Therefore, we will estimate the appropriate sample size based on feasibility instead of on statistics.

### Recruitment

2.7

Twenty-four Participants will be recruited from outpatients in the esophagus-stomach surgery department at Tohoku University Hospital, Sendai, Japan.

### Randomization, allocation, and blinding

2.8

Registration and allocation of the participants will be performed by the investigators and WDB Clinical Research Co., Ltd. The eligible patients will be blindly randomized to either arm P or arm A in a 1:1 ratio. The random sequence will be created using computer-generated permuted block randomization.

### Data collection

2.9

All data will be collected and recorded on a paper-based case report form by the investigators. Patient characteristics, the questionnaires, and evaluation forms such as HADS, EAT-10, ES4, as well as the findings of videofluoroscopy swallowing measurement and CT, abdominal gas volume, laboratory data, and physical status will be collected. Adverse effects will also be recorded. After recording the data, the investigators will confirm the case report form, referring to its source documents.

### Data management

2.10

We will assign all participants identification code numbers. Upon registering and recording the case report form, personal identifying information (e.g., name, address, phone number, medical record number) will be deleted from the data. The linkable anonymized number table will be created and stored by a personal information manager. All data will be kept in locked storage for at least 5 years after study completion. The data management center (WDB Clinical Research Co., Ltd.) will confirm the case report form to check for duplication, missing information, and deviation of data.

### Statistical methods

2.11

The primary statistical analyses will be performed by WDB Clinical Research Co., Ltd. using the full analysis data set, from which patients who withdraw consent before assessment of the primary endpoint will be excluded. In addition, we will repeat the analyses in the per-protocol set, which will exclude patients with major protocol deviation. The safety analysis will be performed using the complete data set in the BRIHK group.

For baseline characteristics variables, summary statistics will be calculated using frequencies and proportions for categorical data; means, standard deviations, medians, and quartiles will be used for continuous values. Patient characteristics will be compared using the Chi-squared test or Fisher exact test for categorical valuables and the Wilcoxon rank-sum test for continuous valuables. For the primary intra-group analysis, we will calculate mean HADS and ES-4 scores for each timepoint with 95% confidential intervals and compare the HADS and ES-4 scores at the baseline with those during the treatment period using Wilcoxon signed-rank test. For the inter-group analysis, we will calculate the change in the HADS and ES-4 scores from the pre- to post-treatment period and compare them between the 2 groups using Wilcoxon signed rank test. Then, we will perform an analysis of covariance with the covariates of patient characteristics and calculate the confidence interval. For the analyses of secondary outcome measures between the 2 groups, we will perform the Chi-squared test or Fisher exact test for categorical valuables and Wilcoxon rank-sum test for continuous valuables. *P* values less than 5% will be considered statistically significant, and we will not adjust *P* values in multiple comparisons.

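### The safety analysis is restricted to the BRIHK group, which contradicts the aim of assessing safety against placebo and leaves adverse events without a concurrent reference

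*Protocol article*

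**What the plan says.** The Abstract (Background) states the objective comparatively: "The aim of this study is to evaluate the efficacy and safety of BRIHK compared to a placebo". The design is described as "This will be a single-center, single blind, placebo-controlled randomized clinical trial". On size and allocation the article says "Twenty-four patients with esophageal cancer undergoing radical resection surgery will be registered to participate" and "The eligible patients will be blindly randomized to either arm P or arm A in a 1:1 ratio". Under Interventions, both arms follow the same schedule and method of administration.

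Under Outcomes, the safety measures are adverse events, side effects of BRIHK, and "laboratory data abnormalities exceeding postoperative change". The same section separately lists aspiration pneumonia, inflammatory markers and laboratory findings among the secondary outcomes.

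Statistical methods then fixes the safety population: "The safety analysis will be performed using the complete data set in the BRIHK group". Later in that section, secondary outcomes are to be compared between the two groups by a chi-squared or Fisher exact test, or by a Wilcoxon rank-sum test. No sentence provides for a between-arm analysis under the heading of safety.

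**The concern.** The safety population is named explicitly and excludes the placebo arm. This is a stated rule, not a detail left to an analysis plan, and an analysis plan that followed it would produce single-arm safety tables.

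Treatment runs from 2 weeks before to 6 weeks after esophagectomy. The Introduction says that morbidity and mortality after this operation remain higher than after other thoracic procedures. Many events in the window are therefore to be expected with no study drug at all. The concurrent placebo arm, with the same operation and schedule, shows how many. Without it, a reader of the safety table cannot tell whether a count in the BRIHK group is high, low or ordinary, and the safety half of the stated aim is not met for adverse events and side effects.

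**Working it through.** There is no plan figure to reproduce, because the sample size rests on feasibility ("we will estimate the appropriate sample size based on feasibility instead of on statistics"). The check is a comparison of sections, followed by arithmetic on what each safety population can show.

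**Step 1: which safety items have a placebo comparison as written?**

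- Aspiration pneumonia: a secondary outcome, so yes, under the between-group rule.
- Laboratory findings and inflammatory markers: secondary outcomes, so yes, as measured values.
- Laboratory abnormalities flagged as a safety measure: covered by the BRIHK-only sentence, so no.
- General adverse events: covered by the BRIHK-only sentence, so no.
- Side effects: covered by the BRIHK-only sentence, so no.

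The Outcomes section labels its safety items as secondary. If that label brings them under the between-group rule, Statistical methods gives two incompatible instructions for the same data. If it does not, the last three items have no comparison. Either way the text needs correcting.

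**Step 2: size of the two safety sets.** Inputs: 24 patients (Abstract) and 1:1 allocation (Randomization, allocation, and blinding).

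- BRIHK only: 24 × 1/2 = 12.
- Both arms: 24.

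Block sizes and dropout could shift the 12 slightly.

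**Step 3: how little a single-arm count says.** Exact (Clopper-Pearson) 95% intervals for 12 patients:

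- 0 of 12: upper limit 1 − 0.025^(1/12) = 26.5%.
- 2 of 12: 2.1% to 48.4%.

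**Step 4: background events with no drug effect (illustration only).** The Introduction gives 9% to 19% for postoperative pneumonia, the one perioperative complication for which it gives an incidence.

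- Expected count: 12 × 0.09 = 1.08 and 12 × 0.19 = 2.28.
- Chance of at least one: 1 − 0.91^12 = 0.678 and 1 − 0.81^12 = 0.920.

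These figures show that a perioperative complication at such a rate will usually appear in 12 patients without any drug effect. They do not measure the harm done by the BRIHK-only rule, because aspiration pneumonia is itself compared between arms.

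**Step 5: what the two-arm table could show.** Two-sided Fisher exact test, 12 against 12:

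- 4 vs 0: 2 × C(12,4)/C(24,4) = 2 × 495/10,626 = 0.093.
- 5 vs 0: 2 × C(12,5)/C(24,5) = 2 × 792/42,504 = 0.037.
- 7 vs 1: p = 0.027.
- 8 vs 2: p = 0.036.

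Only large imbalances would reach p < 0.05, so the comparison is descriptive.

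**The case against.** Five points can be made for the plan.

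- **Part of the ground is already covered.** Aspiration pneumonia and laboratory findings are compared between arms as secondary outcomes. This stands, and it limits the point. A reader might infer that the trial has no placebo reference for any clinical event, or that drug effects can never be separated from surgical ones. The documents do not support that. The gap concerns general adverse events, side effects and abnormalities flagged in the safety analysis.
- **Causality is reviewed case by case.** The Harms section sends adverse-event outcomes to a data and safety monitoring board. That is a real safeguard, but individual attribution does not replace a randomised comparison of frequencies. A reader might also infer that attribution will be made by people who know the allocation. The article says only that participants are blind, and it does not say what the board sees, so that is conjecture.
- **The laboratory criterion may not need a control arm.** The wording about exceeding postoperative change is undefined in the article. It could mean beyond the clinically expected course, and the full protocol may define it. So the placebo arm is the natural reference here, but not one that the wording strictly requires.
- **Twelve per arm is too few to show safety or harm.** This is true of formal testing, as the Fisher results show. It does not argue for dropping the control column. In a table where one or two chance events dominate, the reader needs that column more.
- **The gap can be repaired at reporting.** Data collection and Harms do not limit recording to one arm, so the placebo data should exist. This lowers the severity, but it does not remove the contradiction.

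**Conclusion.** The point holds in this limited form. The BRIHK-only safety sentence contradicts the aim of assessing safety against placebo, and it conflicts, at least on one reading, with the between-group rule for secondary outcomes. If followed, it would report adverse events, side effects and flagged laboratory abnormalities for about 12 patients without a concurrent reference, although about 12 placebo patients on the same schedule are available.

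This rests on two assumptions: the 1:1 split gives close to 12 per arm, and adverse events are recorded in both arms, as Data collection and Harms suggest. The full protocol and any analysis plan were not available, but the sentence is a positive rule that they would have to override.

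The severity is should-fix. Safety is a secondary measure in a trial sized on feasibility, the primary analyses are unaffected, and the corrected comparison would be descriptive.

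**What to change.** Replace the safety sentence in Statistical methods with a safety set of all randomised patients who took at least one dose of BRIHK or placebo, analysed by product received. Tabulate adverse events, side effects and laboratory abnormalities by arm, with risk differences and exact 95% confidence intervals, and state that the comparison is descriptive. Define laboratory change beyond the postoperative course with the placebo arm as the reference. State whether the safety measures also fall under the between-group tests for secondary outcomes, so that the section gives one instruction.

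The cost is a short text change and one more column in the safety tables. Sample size, schedule and data collection do not change. The limit that remains is precision: at about 12 per arm, intervals will be wide and an absence of differences will not demonstrate safety.
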